### Outcome measures

Outcome measures are summarised in Table 5.

**Table 5 T5:** Outcome measures

**Primary outcome measures**	**Data collection instrument**	**Collection points†**
Health-related quality of life	iHOT-33	0, 14, 24 weeks
Function in sport	Sport subscale of HOS	0, 14, 24 weeks
**Secondary outcome measures**		
Symptoms, pain, function in daily living and sport, participation in physical activities hip/groin-related quality of life	HAGOS	0, 14, 24 weeks
Physical function	Activities of daily living subscale of HOS	0, 14, 24 weeks
Activity level	Modified Tegner Activity Scale	0, 14, 24 weeks
Sport participation	Heidelberg Sports Activity Scale	0, 14, 24 weeks
Global rating of overall change	Perceived overall change in hip/groin symptoms compared to baseline – 7 point ordinal scale	14, 24 weeks
**Other measures**		
Patient demographics, past treatment	Questionnaire	0 weeks
Surgical procedure	Post-surgery letter from surgeon to referring doctor	Following surgery
Adverse events	Patient logbook, questionnaire	14 weeks
Other treatments/co-interventions	Questionnaire	14, 24 weeks
Physiotherapy session attendance	Therapist treatment records	During intervention
Medication use	Questionnaire	14 weeks
Home/gym program adherence	Participant log book – number of days/times completed	Daily during intervention
	Self-rated using 11-point numeric rating scale	14 weeks

iHOT-33= International Hip Outcome Tool.

HOS=Hip Outcome Score.

HAGOS=Copenhagen Hip and Groin Outcome Score.

† 0=baseline 2 weeks pre operatively; 14 and 24 weeks are timed from the date of surgery.

#### Patient reported outcomes

The International Hip Outcome Tool (iHOT-33) is a recently developed self-administered tool that measures health-related quality of life in young active patients with hip disorders [23].This 33-item questionnaire covers four domains including: symptoms and functional limitations (16 items); sports and recreational activities (6 items); job related concerns (4 items); and social, emotional and lifestyle concerns (7 items). It uses a 100 mm horizontal visual analogue scale response format with scores ranging from 0 to 100 for each question where a higher score represents better quality of life. The overall score is calculated by taking the average out of 100 for the completed questions. The item relating to sexual activity will be omitted for ethical reasons, due to the inclusion of 16–18 year-olds in this study. For those patients who are not working for reasons other than their hip joint problems, the job-related questions are omitted and the overall score still calculated by taking the average out of 100 for the remaining questions [23]. This tool has good test retest reliability (intraclass correlation coefficient of 0.78), demonstrated face, content and construct validity and is highly responsive to clinical change (effect size of 2.0, standardised response mean of 1.7, responsiveness ratio of 6.7) [23]. In a recent comparison of the reliability of patient reported outcomes for young active adults (mean age 24 years) with FAI, we found the iHOT 33 to have a test retest reliability slightly higher than that previously estimated in an older cohort (intraclass correlation coefficient of 0.92 for total score). It is also one of the patient-reported outcomes that contain the highest number of items of particular relevance to a younger cohort, such as sports and recreation and job-related issues [24].

The Hip Outcome Scale (HOS) is a self-administered questionnaire designed to assess function in patients undergoing hip arthroscopy [1]. It assesses the degree of difficulty in performing tasks in two domains; activities of daily living (ADL, 17 items) and sport (9 items). The items are scored on a five point Likert scale from 4 to 0 with 4 being 'no difficulty’ and 0 being 'unable to do’. The score on each of the items are summed and divided by the highest potential score (68 for the ADL subscale and 36 for the sport subscale) then multiplied by 100 to obtain a percentage. In younger patients undergoing hip arthroscopy, the HOS has excellent test re-test reliability (intraclass correlation coefficient values of 0.92 for the sports subscale and 0.98 for the ADL subscale), evidence of content, construct and concurrent validity [1,25] and is responsive to clinical change (effect sizes of 1.5 and 1.2 for the Sports and ADL subscales, respectively and area under the receiver operating characteristic curves of 0.90 and 0.88) [25]. Although our reliability estimates for the HOS (ICC 0.73–0.9) [24] were lower than those reported in a slightly older (mean age 33 years) cohort of patients following hip arthroscopic surgery (ICC 0.92–0.98 [24]), in two recent systematic reviews of the clinimetric properties of patient-reported outcome questionnaires to assess hip and groin disability, the HOS was recommended by both for evaluating patients undergoing hip arthroscopy [26,27].

The Copenhagen Hip and Groin Outcome Score (HAGOS) is a newly-developed patient-reported questionnaire specifically designed for young to middle-aged, physically active individuals with hip and groin pain [27]. It is a quantitative measure of the person’s hip and groin disability according to the different levels of the International Classification of Functioning. The HAGOS consists of 37 items in six separate subscales relating to the past week, assessing pain (10 items), symptoms (7 items), physical function in daily living (5 items), physical function in sport and recreation (8 items), participation in physical activities (2 items) and hip and/or groin-related quality of life (5 items). Items are scored on a five-point Likert scale of 0 to 4, where 0 indicates no difficulty and 4 indicates extreme difficulty. A normalised score (100 indicating no symptoms and 0 indicating extreme symptoms) is calculated for each subscale. This questionnaire has been shown to have adequate measurement properties in young to middle-aged patients with chronic hip/groin pain including evidence of construct validity, responsiveness to change [27] and good to excellent test-retest reliability (intraclass correlation coefficients 0.82 to 0.91 [27] and 0.79-0.94 for the subscale [24]. Inclusion of the HAGOS will allow us to assess similarity of results from this and other self-reported measures included.

At each re-assessment time, participants will rate their perceived overall change in their hip/groin problem (compared to baseline) on a seven-point ordinal scale (much worse to much better). Scales of this kind are frequently used as an external criterion for comparison with changes in scores of other outcomes [28]. Measuring participant-perceived change using a rating of change scale has been shown to be a clinically relevant and stable method of identifying improvements that are truly meaningful from the individual perspective [29].

A modified Tegner Activity Scale and the Heidelberg Sports Activity Score will be administered to grade participants’ level of physical activity (both sport/recreation and occupational) [30,31].

#### Adherence in the physiotherapy group

The number of physiotherapy visits will be recorded for the PT group. Participants in this group will maintain a log-book to record the frequency, intensity and duration of the exercises in their home/aquatic/gym rehabilitation program. They will also rate their adherence to the home program overall, as well as to its separate components (gym program, pool sessions and home exercises), at 14 weeks post-surgery on 11-point numeric rating scales (with 0 being 'not at all’ to 10 being 'completely as instructed’).

#### Adverse events, co-interventions and medication use

Information on adverse events, co-interventions and medication use will be collected during the intervention phase using a log book in both groups as well as by self report questionnaire at 14 and 24 weeks post surgery. The CON group will record physical activity performed each week (type, duration and intensity), and specifically whether they consulted a physiotherapist following surgery.

### Sample size

The primary endpoint will be change from baseline to 14 weeks post-surgery in (i) the iHOT-33 and (ii) sport subscale of the HOS. The minimum clinically important difference to be detected in this patient population is 6.1 for the iHOT-33 [23] and 6.0 for the Sport subscale of the HOS [24]. Between-participant standard deviations have not been widely reported in the literature for these questionnaires so the study was powered to detect a moderate effect size of 0.5. Given this, the required sample for a two-tailed comparison of the two groups using analysis of covariance with baseline values as covariates, when d = 0.5, power is 0.8 and type I error is 0.05 is 41 participants per group. To allow for a 15% dropout rate a total of 100 participants will be recruited.

### Data and statistical analysis

A biostatistician will oversee the blinded analyses of the data. The primary analysis of the data will be undertaken using the principle of intention-to-treat. This analysis will include all participants including those who have missing data and those who do not fully adhere to the protocol. Some attrition is anticipated despite the fact that we will implement procedures to minimise loss to follow-up and participant withdrawal, and maximise adherence. To account for missing data, multiple imputation of missing follow-up measures, assuming missing data are missing at random and follow a multivariate normal distribution [32] will be performed as a sensitivity analysis.

Demographic and clinical characteristics as well as baseline data will be presented to assess the baseline comparability of the intervention groups. These variables will also be examined for those participants who withdraw from the study and those who remain.

Descriptive statistics will be presented for each group as the mean change (standard deviation, 95% confidence intervals) in the outcomes from baseline to each time point. For continuous outcome measures, differences in mean change will be compared between groups using linear regression random effects modelling adjusted for baseline values of the outcome. Model diagnostic checks will utilise residual plots. Similar regression models for binary and ordinal outcome measures will use random effects logistic and proportional odds models, respectively. We will also perform a per protocol analysis as appropriate.

No statistical adjustment will be made for multiple testing. All tests will be two sided and carried out at the 5% level of significance. Any changes to the study design or analysis plan will be documented with full justification.

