### Study procedure

Patients who are scheduled for hip arthroscopic surgery and fulfil the eligibility criteria will be identified by the surgeon and provided with study information by staff at the surgeon’s practice. An independent research assistant will confirm eligibility via subsequent telephone screening. Consenting participants will complete baseline questionnaires electronically or via post approximately two weeks prior to surgery. Upon receipt of baseline data, participants will be consecutively randomised into either the PT or the CON group by an independent person not involved in recruitment, assessment or treatment of participants. Participants in both groups will undergo hip arthroscopy for management of their FAI as scheduled by their surgeon and will receive standardised pre- and post-operative care, including an in-patient physiotherapy visit, provision of written educational material and a follow-up appointment with the orthopaedic surgeon at approximately two weeks post surgery. The PT group will additionally receive seven individual 30-minute physiotherapy sessions including one pre-operative session and six post-operative sessions at fortnightly intervals commencing two weeks after surgery. The PT group will also perform a home, aquatic and gym rehabilitation program. Re-assessment will occur at 14 weeks (following completion of physiotherapy rehabilitation in the PT group) and 24 weeks post surgery via administration of questionnaires completed online or via post. A flow chart outlining the study procedures is shown in Figure 1.

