### Blinding

It is not possible to blind participants in this study. The study physiotherapists treating participants in the PT group will be, by necessity, unblinded. The researcher managing the patient-completed data will be blinded to group allocation as will the physiotherapists providing in-patient treatment to both groups. The orthopaedic surgeon will also be blinded to group allocation and participants will be asked not to disclose this to the surgeon at their follow-up appointment. The statistician will be blinded to group allocation until completion of the statistical analyses.

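### The one missing-data sensitivity analysis named shares the primary model's implied missing-at-random assumption, so it cannot show robustness to informative dropout; the claim to include everyone is also slightly too wide

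*Protocol article*

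**What the plan says.** All of the analysis text is in the protocol article, section Data and statistical analysis.

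- **Analysis set.** The primary analysis follows intention-to-treat: "This analysis will include all participants including those who have missing data and those who do not fully adhere to the protocol".
- **Primary model.** For continuous outcomes, "differences in mean change will be compared between groups using linear regression random effects modelling adjusted for baseline values of the outcome". No imputation is part of this step, and the missing-data assumption is not written down.
- **Sensitivity analysis.** The method named for missing data is "multiple imputation of missing follow-up measures, assuming missing data are missing at random and follow a multivariate normal distribution".
- **Other attrition check.** Baseline and clinical characteristics are tabulated by withdrawal status: "These variables will also be examined for those participants who withdraw from the study and those who remain".

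Three other sections bear on the point. Blinding says "It is not possible to blind participants in this study". Study procedure has re-assessment at 14 weeks and "24 weeks post surgery via administration of questionnaires completed online or via post". Sample size says "To allow for a 15% dropout rate a total of 100 participants will be recruited".

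**The concern.** A sensitivity analysis is useful when it relaxes an assumption that the main result depends on. Here that assumption is that, given the observed data, people who do not return questionnaires would have scored like those who do. The planned imputation keeps this assumption and changes only the computation.

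The design gives reason to test it. Participants know their allocation and both primary outcomes are self-reported. The physiotherapy (PT) group has seven study visits, while controls (CON) are asked not to undertake formal rehabilitation. The extent of dropout and the reasons for it could therefore differ by arm and could depend on recovery that nobody observes. If the primary model and the imputation agree, the report may present that agreement as robustness although the relevant risk was never examined.

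A smaller matter is the statement that every participant is included. With baseline as a covariate, someone with no follow-up score has no outcome to enter.

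**Working it through.** **Inputs from the article.** 41 per group, 15% dropout and 100 recruited (Sample size); minimum clinically important difference (MCID) 6.1 for the iHOT-33 and 6.0 for the HOS sport subscale (Sample size); design effect 0.5 SD (Sample size); follow-up at 14 and 24 weeks (Study procedure).

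**Step 1: the plan's own figure.** 2 × 41 = 82, and 82 / 0.85 = 96.5, so 97. The article recruits 100, which is consistent. At 15% loss, 100 × 0.85 = 85 supply data. The 41 itself is 62.8 × (1 − ρ²), where 62.8 per arm is the requirement without a covariate. With ρ = 0.6 this is 62.8 × 0.64 = 40.2, so 41. The article does not give ρ. I use 0.6 below as an assumption, and the point does not depend on it.

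**Step 2: the two analyses side by side.**

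| | Primary model | Planned imputation |
|---|---|---|
| Assumption | Missing at random (implied by likelihood fitting) | Missing at random (stated) |
| Distribution | Normal (linear model) | Multivariate normal |
| Extra predictors of missingness | None named beyond baseline | None named |
| People with no follow-up score | Drop out of the model | Retained by imputation |

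The last row is the only clear difference. Imputing those people under missing at random adds almost no information on the group difference.

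**Step 3: simulation.** 600 trials were run for each true effect, with 50 per arm. Assumed correlations were 0.6 (baseline to each follow-up) and 0.75 (14 to 24 weeks). Eight per arm had no follow-up (15% of 50 = 7.5, rounded up), so 84 of 100 entered the primary model. In the PT arm, worse outcomes were more likely to be missing. In the CON arm, loss was random. No auxiliary variables were used.

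| True effect (SD) | Full data | Random-effects model | Imputation under missing at random |
|---|---|---|---|
| 0.50 | 0.51 | 0.62 | 0.62 |
| 0 | 0.01 | 0.11 | 0.11 |

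The two planned estimates correlated at 0.99 across trials, with a mean absolute difference of about 0.014 SD. In this set-up, imputation carries over the primary model's bias of about 0.1 SD.

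**Step 4: size of a departure.** Let m be the fraction missing in an arm, and δ the amount by which the unseen scores differ from their missing-at-random prediction. The group difference (PT minus CON) then moves by

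shift = m_PT × δ_PT − m_CON × δ_CON.

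The δ values are assumptions. 6 and 12 points are about one and two MCIDs.

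| Missing PT / CON | δ PT / CON (points) | Shift (points) |
|---|---|---|
| 15% / 15% | −6 / 0 | 0.15 × (−6) = −0.9 |
| 15% / 15% | −12 / 0 | 0.15 × (−12) = −1.8 |
| 15% / 15% | −6 / −6 | −0.9 + 0.9 = 0 |
| 5% / 25% | −6 / −6 | −0.3 + 1.5 = +1.2 |
| 5% / 25% | 0 / −12 | 0.25 × 12 = +3.0 |

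Against an MCID of 6.0, 0.9 / 6.0 = 15% and 1.8 / 6.0 = 30%. On the SD scale, a departure of 0.5 or 1 SD confined to one arm with 15% missing gives 0.15 × 0.5 = 0.075 or 0.15 × 1 = 0.15 SD. These are again 15% and 30% of the design effect of 0.5. A 1 SD departure confined to an arm with 25% missing gives 0.25 SD, half the design effect.

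**The case against.** **The article is a condensed text.** It never says that imputation is the only sensitivity analysis, and an analysis plan that is not shown may contain more. That stands, so the absence of a departure-from-random analysis is not itself the fault. The point rests on what the article does fix: it gives the missing-data check a method and an assumption, and that assumption does not vary the one at risk.

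**The shared assumption is partly inferred.** The primary model's assumption is not written, and the structure of the random effects is not given. If 14 weeks were modelled alone, imputation using the 24-week score would rest on a somewhat different condition. Imputation could also use surgical findings or other collected variables. This stands as a limit. A reader might infer that imputation must give the same answer and is worthless; the documents do not support that. The near-identity in the simulation belongs to a set-up with both visits lost and no auxiliary variables.

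**Missing both visits.** A reader might infer that up to 15 of 100 participants contribute nothing. That requires every dropout to miss both questionnaires. If the two times are modelled jointly, anyone with one score contributes, and the 15% is only a sample-size allowance.

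**Ordinal outcomes.** The article also says "Similar regression models for binary and ordinal outcome measures will use random effects logistic and proportional odds models", and a reader might infer that normal imputation would break those models. The text does not say how ordinal outcomes would be imputed, and imputed values can be rounded to categories. This is analysis-plan detail for secondary outcomes and is not part of the point.

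**The mechanism is softened.** People who want formal supervised rehabilitation are excluded (Participants), retention procedures are planned, and those who withdraw are compared with those who remain. The first two reduce the risk. The comparison can show baseline differences but cannot test dependence on unseen outcomes.

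**Conclusion.** The point holds in a limited form. The named sensitivity analysis makes essentially the assumption that the primary model already implies. Without informative auxiliary variables it will largely repeat the primary estimate and cannot show robustness to informative dropout. The analysis-set statement is too wide only for participants with neither the 14- nor the 24-week score.

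The size is modest: about 0.9 to 1.8 points, or 15% to 30% of the MCID, with 15% missing and a departure of 6 to 12 points in one arm. It is larger if dropout is unequal between arms, and zero if dropout and departures are equal. These figures rest on assumed departures, a likelihood-fitted model and, for the simulation, assumed correlations.

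A reader might conclude that the trial's result will be biased. The documents do not show that dropout will be informative. They show only that the stated check could not reveal how much it would matter. This is a cheap improvement, not a flaw that invalidates the primary analysis.

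**What to change.** Keep the primary model and the planned imputation, and make three changes.

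1. State that the primary model assumes missing at random.
2. Describe the primary analysis set as all randomised participants with at least one follow-up score, analysed as randomised.
3. Add a delta-adjusted imputation for the iHOT-33 and the HOS sport subscale at 14 weeks. Worsen the imputed scores by, for example, 0 to 12 points (about two MCIDs), in PT only, in CON only and in both, and report where the conclusion changes. The range is a suggestion and should be justified in advance. Such an analysis does not detect informative dropout; it shows how strong it would have to be to matter.

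The cost is a little extra code and one table, with no new data. The downside is that the conclusion may look less robust. The article already provides for documented and justified changes to the analysis plan.

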### Participants

100 men and women aged 16–35 years with symptomatic FAI who are scheduled for hip arthroscopy will be recruited from the surgical practices of five orthopaedic surgeons in metropolitan Melbourne, Victoria, Australia.

People will be eligible if they have (i) had hip/groin symptoms for at least 3 months; (ii) been diagnosed with FAI by an orthopaedic surgeon based on symptoms, clinical signs and imaging findings; and (iii) are scheduled for hip arthroscopy.

People will be excluded from participating if they (i) have radiographic evidence of hip osteoarthritis that is more than mild in severity defined as Tonnis > grade 1 [16]; (ii) are a professional athlete; (iii) have other concurrent injury/conditions that will affect their ability to participate in the rehabilitation program and/or assessment procedures; (iv) are unable to attend a study physiotherapist or participate in the rehabilitation program if randomised to the PT group; (v) wish to undertake formal supervised rehabilitation following hip arthroscopy; and (vi) are unable to understand English.

Ethical approval has been obtained from the University of Melbourne Human Research Ethics Committee (HREC No. 1238190). All participants will provide written informed consent.

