### Randomisation and allocation concealment

The randomisation schedule will be prepared by the study biostatistician using a computer-generated random numbers table. There will be a 1:1 allocation ratio of participants to the PT and CON groups. Randomisation will be conducted by random permuted blocks of varying size, and stratified by orthopaedic surgeon (so that each surgeon contributes approximately equal numbers in each group to control for surgical variation) as well as by whether the participant is having unilateral or bilateral surgery. Participants in the PT group will choose their preferred project physiotherapist according to geographical convenience.

Consecutively numbered, sealed, opaque envelopes containing group allocation will be prepared by a researcher with no other involvement in the study. The envelopes will be stored in a locked location and will be opened in sequence to reveal group allocation by a researcher not involved in recruitment, treatment or assessment of outcomes.

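### Neither stratification factor is named in the analysis model: unilateral/bilateral surgery is absent, and surgeon is covered only if it is one of the unidentified random effects, so some precision may be forgone

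*Protocol article*

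**What the plan says.** **Design.** Under Randomisation and allocation concealment, permuted blocks are "stratified by orthopaedic surgeon (so that each surgeon contributes approximately equal numbers in each group to control for surgical variation". The same sentence then adds laterality as a second factor: "as well as by whether the participant is having unilateral or bilateral surgery". Participants are "recruited from the surgical practices of five orthopaedic surgeons in metropolitan Melbourne", so there are up to 5 × 2 = 10 strata. Allocation is equal: "There will be a 1:1 allocation ratio of participants to the PT and CON groups".

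**Analysis.** Under Data and statistical analysis, for continuous outcomes, "differences in mean change will be compared between groups using linear regression random effects modelling adjusted for baseline values of the outcome". Binary and ordinal outcomes get random effects logistic and proportional odds models of the same kind. The section does not say which units carry the random effects.

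**Sample size.** The calculation assumes a comparison "using analysis of covariance with baseline values as covariates" and states that the number needed "when d = 0.5, power is 0.8 and type I error is 0.05 is 41 participants per group". This is the same adjustment set, again without either stratification factor.

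**The concern.** Stratified blocks make the groups nearly equal within each surgeon and each type of surgery. Differences between strata therefore contribute little to the true sampling variance of the treatment difference. A model without stratum terms does not know this: it leaves the between-stratum variation in the residual and counts it as noise. If the strata are prognostic, the reported standard error overstates the real uncertainty, confidence intervals are wider than they need be, and the test rejects too rarely under the null.

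The design section gives control of surgical variation as the reason for stratifying by surgeon, yet the article states its adjustment set twice without that factor. What is at stake is precision that the design has already paid for, in a trial of 100 people.

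**Working it through.** **Inputs from the article:** d = 0.5, power 0.80, two-sided 5% ("All tests will be two sided and carried out at the 5% level of significance"), 41 per group, 100 recruited with 15% dropout, five surgeons, two types of surgery.

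**Inputs not in the article (assumptions):** the correlation ρ between baseline and follow-up, and R², the share of residual variance (after baseline adjustment) that the strata explain. R² is taken from 0 to 0.30.

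**Step 1: the plan's own figure.** n per group = 2(1.960 + 0.842)²(1 − ρ²)/d² = 62.8(1 − ρ²).
- ρ = 0: 63 per group.
- ρ = 0.5: 48 per group.
- ρ = 0.6: 62.8 × 0.64 = 40.2, so 41 per group.
- ρ = 0.7: 33 per group.

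The stated 41 is reproduced with ρ of about 0.6, which is used below. With 15% dropout, 82/0.85 = 96.5, so 97; the plan recruits 100.

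**Step 2: with and without stratum terms.** Take the outcome SD as 1. The residual variance after baseline adjustment is 0.64, so the SE reported without stratum terms is √(2 × 0.64/41) = 0.1767. With exact balance within strata, the true SE is 0.1767 × √(1 − R²). Then:
- reported SE too large by a factor of 1/√(1 − R²);
- type I error without stratum terms = 2[1 − Φ(1.96/√(1 − R²))];
- power without stratum terms = 1 − Φ[(1.96 × 0.1767 − 0.5)/(0.1767√(1 − R²))];
- power with stratum terms = Φ[0.5/(0.1767√(1 − R²)) − 1.96].

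Example, R² = 0.10: the true SE is 0.1767 × 0.9487 = 0.1676. Without terms, (0.3463 − 0.5)/0.1676 = −0.917, giving 82.0%. With terms, 0.5/0.1676 − 1.96 = 1.023, giving 84.7%.

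| R² | Reported SE too large by | Type I error without terms | Power without terms | Power with terms |
|---|---|---|---|---|
| 0 | 0% | 5.0% | 80.8% | 80.8% |
| 0.05 | 2.6% | 4.4% | 81.4% | 82.7% |
| 0.10 | 5.4% | 3.9% | 82.0% | 84.7% |
| 0.20 | 11.8% | 2.8% | 83.5% | 88.6% |
| 0.30 | 19.5% | 1.9% | 85.1% | 92.3% |

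**Step 3: simulation with imperfect balance.** 3,000 trials per setting: 100 randomised, 15% random dropout, surgeon shares of 40/20/20/10/10%, 15% bilateral, blocks of 4 or 6, ρ = 0.6. Of the strata variance, 80% came from surgeon and 20% from laterality. Each trial was analysed by ordinary least squares.

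| R² | Type I error without / with terms | Power without / with terms |
|---|---|---|
| 0 | 5.3% / 5.5% | 81.0% / 80.4% |
| 0.05 | 4.7% / 4.9% | 80.0% / 80.6% |
| 0.10 | 4.2% / 5.1% | 81.7% / 84.3% |
| 0.20 | 2.8% / 4.3% | 81.9% / 87.5% |
| 0.30 | 2.8% / 5.0% | 83.3% / 91.7% |

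Monte Carlo error is about 0.7 points for power, √(0.8 × 0.2/3000), and 0.4 points for type I error, √(0.05 × 0.95/3000). The pattern agrees with step 2. The SE excess is smaller than the formula gives, because incomplete blocks and dropout spoil exact balance. At R² = 0.20 the mean reported SE was 0.1746 against an empirical SD of 0.1612, which is 8.3% too large rather than 11.8%.

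**The case against.** **The random effects might include surgeon.** The article does not identify them. Participant is a natural reading with follow-up at 14 and 24 weeks, but surgeon or treating physiotherapist is possible. This stands: one cannot say that surgeon is left out, only that it is not named. It does not rescue laterality, which is mentioned only under randomisation.

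**The full covariate list may sit in an analysis plan that is not shown.** That is possible, and silence alone would be no finding. But the article is not silent: it states an adjustment set in two places, and both give baseline only. It also promises to document and justify any change to the analysis plan, so the stated model reads as the commitment.

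**The harm is conditional.** This stands. The documents give no surgeon intraclass correlation, no bilateral share and no SD. One set of operative rules and standardised perioperative care for all participants are reasons not to presume large surgeon effects. At R² = 0.05 the gain is about one point of power.

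**Stronger readings.** A reader might infer that the standard errors are certainly too large, that stratification has been wasted, that the trial is underpowered because of this, or that its type I error is inflated. None is supported. The first needs prognostic strata. Balance is kept whatever the model, and power without stratum terms itself rises with R² in the step 2 table, so part of the benefit survives. The sample size already assumes a baseline-only model. The error is on the conservative side.

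**Conclusion.** The point holds as a mismatch between the randomisation design and the stated analysis. It is clear for unilateral/bilateral surgery and unresolved for surgeon until the random effects are identified. On the closed-form calculation with ρ of about 0.6 and 41 per group, the power forgone is about 1 point at R² = 0.05, 3 points at 0.10, 5 points at 0.20, and none at 0. Type I error falls below 5% as R² rises. R² is an assumption throughout, and the SE excess and type I figures lean to the high side of the effect because they take balance within strata as exact.

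Validity is not threatened: the estimate is unbiased, and the planned 80% power is not breached by this omission. The change is still worth making. Adjustment costs almost nothing if the strata prove uninformative (simulated power 80.4% against 81.0%) and gains several points if they are moderately prognostic.

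**What to change.** In the primary linear model, for both the iHOT-33 and the HOS sport subscale, include group, baseline score, surgeon and unilateral/bilateral surgery, with the 14-week group contrast as the primary estimate. Enter surgeon as four indicators, or as a random intercept if some surgeons enrol few. State which units carry the random effects.

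Main effects are enough. With about 85 completers over up to 10 strata, the average is 8.5 per stratum, and some bilateral strata may be nearly empty.

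In the logistic and proportional odds models, include the strata only where cell counts allow, for example laterality plus a surgeon random intercept. Say there that the odds ratio is then conditional on those terms, and so is not the same quantity as the unadjusted one.

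**Cost:** one or two sentences and no new data, since both factors are known at randomisation. With surgeon as indicators, it uses 4 + 1 = 5 of roughly 80 degrees of freedom.
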